### Eligibility Criteria and Recruitment

All participants will be CSPs employed at partner community health agencies, including Latino Health Access (LHA), Dignity Health, and other agencies, to be recruited throughout our enrollment period. Participating agencies and CSPs will serve HL communities and will be located throughout the United States. Inclusion criteria include being aged ≥18 years and working (for payment or as a volunteer) as a CSP serving low-income HL families. Given that this pilot study is intended to test RS on a new population, we identified a sample size (n=80) that would allow us to identify a signal but not a statistically significant (P<.05) effect. This study aimed to generate a pilot study that could be used to support an adequately powered randomized controlled trial.

Participants will be recruited both offline and via email through their agencies, which will post advertisements in English and Spanish at their facilities, announce the opportunity in staff meetings and via email, and facilitate introductions between the research team and the CSPs. Interested participants will contact research personnel.

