### Randomization and Overview

In this randomized controlled waitlist design (ClinicalTrial.gov identifier NCT05560893), the CSPs will be randomly assigned to an experimental group or a waitlist group. Both groups will complete an identical assessment battery (assessing health behaviors and psychological well-being) and complete stressor tasks (assessing cardiometabolic risk) before the intervention, after the intervention, and at a 3-month follow-up. The experimental group will receive the RS intervention (4 sessions, 1/wk) 1 week after the baseline assessment (Figure 1). The waitlist group will complete the baseline assessment, wait 4 weeks, complete a second baseline assessment, and 1 week later receive the RS intervention. After completing the RS intervention, the participants in both the experimental and waitlist groups will complete the postintervention assessment 1 week later and a follow-up 3 months later.

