### Data Analytic Plan

Descriptive statistics will be used to analyze the demographic characteristics of our sample population. A series of analyses of covariance will be conducted to examine the effects of RS on HRV, health behavior, psychological well-being, threats to CSPs leaving the workforce, and the reach of CSPs’ cardiometabolic health programming. We will compare outcomes at baseline, immediately postintervention, and at the 3-month follow-up across participants in the experimental versus waitlist group. HRV at baseline will be included as a covariate in analyses examining HRV, and all analyses will examine a range of potentially confounding covariates for potential use in analyses (eg, age, BMI, and socioeconomic status; those that are significantly associated with key study variables will be included as covariates in hypothesis testing). Effect sizes will be examined in all analyses. With a sample size of 80, it will be possible to detect small-to-moderate effects (yielding an effect size *d*=0.24) of RS on the CSPs’ cardiometabolic health, threats of CSPs leaving the workforce, and the delivery of cardiometabolic health programming. As stated in the *Eligibility Criteria and Recruitment* section, our goal is not to detect statistically significant effects but rather to look for effect sizes to inform future studies.

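### Covariates are chosen by significance in the trial data from an open list, and a baseline covariate is fixed only for HRV, so the pilot's effect sizes depend on which covariates pass

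*Protocol article*

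**What the plan says.** The relevant text is in the Data Analytic Plan of the protocol article. The model is an analysis of covariance for each outcome: "A series of analyses of covariance will be conducted to examine the effects of RS on HRV, health behavior, psychological well-being", followed by workforce threats and programme reach. One covariate is fixed in advance: "HRV at baseline will be included as a covariate in analyses examining HRV". For everything else, "all analyses will examine a range of potentially confounding covariates for potential use in analyses (eg, age, BMI, and socioeconomic status" are given as examples, and the selection rule is "those that are significantly associated with key study variables will be included as covariates in hypothesis testing".

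Two other sections matter. Under Randomization and Overview, "the CSPs will be randomly assigned to an experimental group or a waitlist group". Under Eligibility Criteria and Recruitment, the purpose of the sample size is described: "we identified a sample size (n=80) that would allow us to identify a signal but not a statistically significant (P<.05) effect". The Data Analytic Plan repeats that the aim is effect sizes for later studies. No unadjusted or fixed-covariate main analysis is described anywhere in the article.

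**The concern.** The covariates are screened as possible confounders, but allocation is random. Randomisation removes systematic confounding. What remains is chance imbalance, and that is best handled by adjusting for variables named beforehand as likely to predict the outcome, whatever their p-value in 80 people.

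The rule decides the model from the same data that give the treatment effect. It is run over many outcomes and can return a different set for each. It does not say whether a covariate must be associated with the outcome, the arm or both, and these have different consequences.

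HRV has a guaranteed baseline covariate. Sleep, diet, exercise, burnout and job satisfaction do not, although the Primary Outcomes and Secondary Outcomes sections have them measured before the intervention. Since the trial exists to supply effect sizes for a larger trial, the question is how far the rule can move those effect sizes and how wide it makes their uncertainty.

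**Working it through.** **Inputs.** N=80 (Eligibility Criteria and Recruitment). Equal arms of 40 are assumed, because no ratio is stated. The threshold p<0.05, the number of candidate covariates (three to six) and their correlations with the outcome (0.1 to 0.3, mutually independent) are also assumed, because the article gives none.

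**The plan's own figure.** "With a sample size of 80, it will be possible to detect small-to-moderate effects (yielding an effect size" is followed by d=0.24. For a plain two-arm comparison the detectable effect at 80% power, two-sided 5%, is (1.96 + 0.842) × √(2/40) = 0.63, so 0.24 is not reproduced from the stated inputs. That is a separate matter. Here 0.24 serves only as a yardstick.

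**Chance that a real predictor is kept when screened against the outcome.** The sample correlation must reach t/√(78 + t²) with t = 1.99, which is 0.22. By Fisher's z, P(kept) = 1 − Φ(1.96 − atanh(r)√77) + Φ(−1.96 − atanh(r)√77).

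| True r | P(kept) |
|---|---|
| 0.1 | 14% |
| 0.2 | 43% |
| 0.3 | 78% |
| 0.4 | 96% |
| 0.5 | 99.8% |

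With three covariates at r=0.2, at least one is dropped with probability 1 − 0.428³ = 92%. At r=0.3 it is 1 − 0.775³ = 53%. In simulation with three covariates at r=0.2, all eight possible sets occurred.

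**How far the estimate moves.** In simulated trials with three to six covariates at r=0.1 to 0.3, the effect from the selected set differed from that of the full fixed set with an SD of about 0.04 to 0.07 outcome SDs. Relative to d=0.24 that is 0.04/0.24 = 17% to 0.07/0.24 = 29%.

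**Precision and type I error when the rule is applied mechanically to the outcome.**

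| Covariates | SE, fixed set | SE, selected set |
|---|---|---|
| three, r=0.1 | 0.227 | 0.224 |
| three, r=0.2 | 0.215 | 0.213 |
| three, r=0.3 | 0.195 | 0.198 |
| six, r=0.3 | 0.159 | 0.166 |

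The largest loss is 0.166/0.159, about 4%. With three covariates it is at most 0.198/0.195, about 1.5%. Type I error was 4.6% to 5.4%.

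**Precision if the screen is against arm.** Under randomisation each covariate passes only 5% of the time, so at least one of three enters in 1 − 0.95³ = 14% of trials. The analysis is then close to unadjusted, for which the SE is √(2/40) = 0.224. For three covariates at r=0.3 the simulated SE was 0.217 against 0.195 for the fixed set, which is 11% larger.

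**If the discretion is used to choose among sets.** The mean range of d over all subsets was 0.11 (three at r=0.2), 0.16 (three at r=0.3) and 0.22 (six at r=0.2). Picking the best-looking set gave 8.3%, 9.4% and 14.8% false positives.

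**Value of a guaranteed baseline.** Adjustment multiplies the SE by √(1 − r²). For an assumed baseline correlation of 0.5 this is 0.866 (13% lower). For 0.7 it is 0.714 (29% lower).

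**The case against.** The strongest reply is that the rule does little damage. Weak covariates are the ones often dropped and they carry little information, while those at r=0.4 or above are nearly always kept. The shift of 0.04 to 0.07 is small beside a standard error of about 0.20 to 0.22. The most useful covariate for HRV is already fixed. All of this stands. So a reader who infers from the dropped covariates that the trial loses material precision goes further than the numbers allow, unless the screen is against arm.

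A reader might also infer that the plan inflates false positives to 8% to 15%, or lets d range over 0.11 to 0.22. The article does not support that: it selects on association with study variables, not on the treatment result. Those figures apply only if someone uses the rule's looseness to choose among sets.

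A complete covariate list, the threshold and the definition of the screening target may sit in an analysis plan not shown, and their absence from an article is no fault. But selection by significance is stated outright, and an analysis plan consistent with the article would keep it.

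If each outcome's baseline value is among the screened candidates, it would almost always pass (99.8% at r=0.5), and most of the 13% to 29% gain would come anyway. The article does not say that it is a candidate. Finally, different outcomes may properly have different predictors. That is an argument for naming them in advance, not for screening.

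**Conclusion.** The point holds as a moderate one that should be changed. The stated rule is unnecessary in a randomised comparison, makes the effect size depend on which covariates pass (SD of the shift about 0.04 to 0.07), and is loose enough to permit model choice after the results are seen. It guarantees baseline adjustment for HRV alone. Applied mechanically against the outcome, it neither inflates type I error nor costs more than a few per cent of precision. Screened against arm, it raises the SE by about 11% in the example above.

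The pilot purpose does not remove the point, because the effect size is the quantity to be handed on. The sizes rest on equal arms, p<0.05 as the threshold, three to six independent covariates at r=0.1 to 0.3, and assumed baseline correlations of 0.5 to 0.7. None of these is given in the article.

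**What to change.** Replace the screening sentence with a covariate set named before analysis begins:

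- each outcome's own first-visit baseline value, for every outcome that has one. The first visit is common to both arms, whereas only the waitlist group has a second baseline;
- a short fixed list drawn from the covariates the protocol already names (age, BMI, socioeconomic status);
- recording device for HRV, since the Primary Outcomes section allows either an arm-worn or a chest-worn device.

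State that no covariate enters or leaves on the strength of a significance test, and report any other set as a sensitivity analysis only.

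The cost is wording. One or two degrees of freedom may go to weak covariates. With three covariates at only r=0.1 the fixed set has an SE of 0.227 against 0.224 for the screened one, about 1% worse.

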**Methods:**

We will recruit a sample of 80 CSPs from community health agencies serving low-income HL populations. Participating CSPs will be randomized into an experimental or a waitlist control. Participants will complete 1 or 2 baseline assessment batteries (before the intervention), depending on the assigned group, and then complete 2 more assessment batteries following the 4-week RS intervention (after the intervention and at a 3-mo follow-up). The RS intervention consists of guided reflections on positive moments of connection with others. Electrocardiogram data will be obtained from a wearable device (Polar Verity Sense or Movisens) to measure heart rate variability. The primary outcome is cardiometabolic health, consisting of cardiometabolic risk (obtained from heart rate variability) and cardiometabolic health behaviors. The secondary outcomes include CSPs’ threats to leaving the workforce (assessed via psychological well-being), intervention acceptability, and CSPs’ delivery of cardiometabolic health programming to the community (exploratory). Analyses of covariance will be used to examine the effects of RS on cardiometabolic health and on CSPs’ threats to leaving the workforce, comparing outcomes at baseline, postintervention, and at follow-up across participants in the experimental versus waitlist group.

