### Objectives

This study aims to analyze the effects of an RS intervention on (1) HL CSPs’ cardiometabolic health (cardiometabolic risk and health behaviors) and (2) the risks of CSPs leaving the workforce. We hypothesize that compared with participants assigned to the waitlist control condition, those in the RS condition will exhibit the following health improvements:

1a. Exhibit lower cardiometabolic risk (lower heart rate variability [HRV]) during a discrimination stressor task1b. Report more favorable cardiometabolic health behaviors pertaining to sleep, exercise, and diet2a. Show reduced threats to CSPs leaving the workforce (greater work satisfaction and psychological agency and lower burnout)2b. Exploratory hypothesis: That introduction of the RS intervention into agencies will result in greater engagement, as evidenced by the following: agencies will show increases in their demonstrated reach to community members through their health programing (ie, fewer absent days, more health-related events offered, larger community attendance at their events, and larger retention of community members in their programs) during the period following the introduction of RS as compared with the 6 months preceding the introduction of RS

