## Results

We expect that 80 CSPs will complete this study. The study was approved by the institutional review board in July 2022. CSPs from community agencies began participating in the study in October 2022, with 79 CSPs enrolled by November 2023. The data collection process is expected to continue until May 2024 and will include participants from LHA, Dignity Health, Green Madison Park, Orange County Health Promoters, and potentially from additional partner community agencies serving low-income HL communities. Transcription; coding; physiological data processing; and data cleaning, reduction, and analysis will occur throughout the following months and after the completion of data collection (Figure 2). We expect to publish our findings during the fourth quarter of 2024.

We will answer our central research questions using statistical analyses. In addition to these central analyses, we anticipate using qualitative methods to examine savoring sessions and discrimination SOC recordings for the themes that emerge (eg, nature of work, sources of strength or stress, and recurring topics). These qualitative analyses have the potential to reveal important information about HL CSPs, an understudied and important population.

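### The statement that 80 participants can detect d=0.24 is wrong under the stated design and conflicts with three other statements in the protocol

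*Protocol article*

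**What the plan says.** The Data Analytic Plan states: "With a sample size of 80, it will be possible to detect small-to-moderate effects (yielding an effect size" d=0.24). It applies this to three outcome groups: cardiometabolic health, threats of leaving the workforce, and delivery of health programming. It does not say what power, sidedness, allocation ratio or baseline-outcome correlation lies behind the figure. The next sentence says that the goal is to look for effect sizes for future studies, not to reach statistical significance.

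Eligibility Criteria and Recruitment gives the reason for the sample size: "we identified a sample size (n=80) that would allow us to identify a signal but not a statistically significant (P<.05) effect". It describes the study as a pilot to support an adequately powered trial.

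The Secondary Outcomes section says that the data on programme delivery will not allow differences between the intervention and waitlist groups to be detected.

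The number 80 is used in two senses. The abstract has "We will recruit a sample of 80 CSPs from community health agencies serving low-income HL populations", and the Results section has "We expect that 80 CSPs will complete this study".

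**The concern.** A claim that a given effect can be detected with a given sample size can be checked, and this one looks far too favourable. With two arms sharing 80 participants, a between-arm difference of a quarter of a standard deviation is close to the standard error of the estimate. The hypotheses are between-arm: "compared with participants assigned to the waitlist control condition, those in the RS condition will exhibit the following health improvements".

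The study's declared product is effect sizes for planning a larger trial. A stated sensitivity of 0.24 misdescribes how precisely those effect sizes will be known. It also sits beside statements elsewhere in the article that say the opposite, so a reader cannot tell what the sample was chosen to achieve.

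**Working it through.** **Inputs.** From the article: total N=80; d=0.24, so the standard deviation is 1; two randomised arms; analysis of covariance, with baseline adjustment stated only for heart rate variability. The 5% level appears only as a threshold that the study is not meant to reach. Assumed, because not stated: 1:1 allocation (40 per arm), two-sided testing, 80% power as the meaning of detectable, no dropout, and a baseline-outcome correlation r of 0.5 to 0.7 for adjusted figures. Equal allocation and no dropout favour the plan.

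**The plan's own figure.** Unadjusted, d=0.24 is not reproduced.

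- Standard error of d: √(1/40 + 1/40) = √0.05 = 0.224.
- Noncentrality at d=0.24: 0.24/0.224 = 1.07.
- Power, noncentral t on 78 df, two-sided 5%: 18.5% (normal approximation 18.8%; one-sided 28.1%).
- Detectable d at 80% power: (1.960 + 0.842) × 0.224 = 0.626 by the normal approximation, 0.634 by exact t. At 50% power it is 0.44.
- Participants needed for d=0.24 at 80% power: 2 × (1.960 + 0.842)² / 0.24² ≈ 273 per arm (274 by exact t), about 548 in total.

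**With baseline adjustment.** The standard error is multiplied by √(1 − r²).

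| Assumed r | Power at d=0.24 | Detectable d, 80% power | 95% CI half-width |
|---|---|---|---|
| 0 (unadjusted) | 18.5% | 0.63 | 0.44 |
| 0.5 | 23% | 0.55 | 0.38 |
| 0.7 | 32% | 0.45 | 0.31 |
| 0.8 | 42% | 0.38 | 0.26 |

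The half-width is 1.96 × 0.224 × √(1 − r²). For 0.24 to be detectable with 80% power, 0.634 × √(1 − r²) = 0.24 is required, which gives r ≈ 0.93 (about 0.90 if one-sided).

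**Other readings tried.**

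- 80 per arm instead of 80 in total: power 33%.
- One-sided test at the 20% level, 40 per arm: detectable d at 80% power 0.38.
- Uncontrolled paired comparison in all 80: power 56%, detectable standardised mean change 0.32.
- 0.24 taken as Cohen's f (d=0.48): power 56%.
- Group-by-time F test with three time points: twice the detectable f comes near 0.24 if the correlation between time points is set at about 0.65. That is an interaction effect size, not a between-arm d, and it is not the stated analysis of covariance.

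**Internal consistency.** Three conflicts need no assumed inputs:

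1. Eligibility Criteria and Recruitment says that 80 will not give a significant effect, while the Data Analytic Plan says that 80 can detect a small-to-moderate one.
2. The sentence after the claim disowns the aim of detecting significant effects.
3. Secondary Outcomes says that between-arm differences in programme delivery cannot be detected, while the Data Analytic Plan includes programme delivery in the d=0.24 claim.

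**The case against.** The best defence is that this is a pilot and says so. The sentence directly after the claim disclaims significance testing and refers back to the sample-size rationale, where the aim is to find a signal. On that reading, 80% power at 5% is a standard the authors never adopted. If the true d were 0.24, the estimate would have the right sign about 86% of the time (0.24/0.224 = 1.07 standard errors). This stands as a point about framing: the choice of 80 is not at fault. It does not rescue the number. The article states no criterion under which 0.24 follows. If detecting means estimating, an observed 0.24 would carry a 95% interval of about −0.20 to 0.68 unadjusted, or −0.07 to 0.55 at r=0.7.

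It is also fair to say that 19% and 0.63 rest on assumed inputs and that the planned model is analysis of covariance. The adjusted range is the fairer one for heart rate variability, the only outcome for which baseline adjustment is stated. It is still about twice 0.24.

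A reader might infer more than the article supports:

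- *That the trial cannot tell 0.24 from 0.6.* This holds unadjusted, but at r=0.7 the upper limit is about 0.55.
- *That a null result will be read as excluding effects above 0.24.* Two sections warn that the study is not designed for significance.
- *That only 64 to 74 participants will be analysable.* This would come from applying 27/34 or 34/37 from the May 2023 counts to 80. Those counts are a snapshot of a running study and mix dropout with participants still in progress.

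**Conclusion.** The d=0.24 statement is wrong as written. Under 1:1 allocation, a two-sided 5% test and no dropout, power at that effect is about 19% unadjusted and about 23% to 32% adjusted at an assumed r of 0.5 to 0.7. The effect detectable with 80% power is 1.9 to 2.6 times the stated figure (0.45/0.24 to 0.63/0.24). Only a baseline correlation of about 0.93 would make the claim true for the stated analysis, and nothing in the article supports one. The three internal conflicts stand whatever inputs are assumed; the one on programme delivery is the most direct.

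The error is confined to the detectability statement. It does not show that the pilot is too small for its declared purpose.

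**What to change.** In the Data Analytic Plan, delete the d=0.24 claim and remove programme delivery from the sentence, so that it agrees with Secondary Outcomes. Replace it with a precision statement that fits the pilot aim and shows its inputs, for example:

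*With 80 participants analysed (40 per arm), the between-arm d will be estimated with a 95% CI half-width of about 0.44 unadjusted; for outcomes adjusted for baseline, about 0.38 to 0.31 if the baseline-outcome correlation is 0.5 to 0.7 (assumed). The effect detectable with 80% power at two-sided 5% would be about d=0.63 unadjusted (0.55 to 0.45 adjusted under the same assumption).*

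Report each effect size with its 95% CI. Say whether 80 means enrolled or completing, and recompute the figures if fewer than 80 are analysed; the Limitations section already expects some missing ECG data. As an illustration only, 34 per arm would give an unadjusted detectable d of 0.69.

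The cost is a less favourable stated figure. Sample size, conduct and planned analyses do not change.

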#### Secondary Outcomes

Secondary outcomes include threats to CSPs leaving the workforce, which will be assessed via psychological well-being (ie, agency, burnout, and job satisfaction) and intervention acceptability. For these secondary outcomes, we will use the Brief Symptom Inventory-18 [46], the Self-Assessment Manikin [47], the Inclusion of Other in the Self Scale–Community Version (IOS-C) [48], the COVID-19 Burnout Scale [49], the Maslach Burnout Inventory [50], the Traumatic Life Events Questionnaire [51], and the Job Satisfaction Survey [52]. RS intervention acceptability and savoring uptake will be assessed via self-developed questionnaires. All these will be assessed before the intervention, after the intervention, and at the 3-month follow-up.

Finally, the CSPs’ delivery of cardiometabolic health programming to the community will be measured in an exploratory manner. This will be assessed via the number of days the CSPs worked, the number of health-related events offered, the retention of community members in the programs offered by the CSPs, and the number of community members attending the events. Data from the time following the introduction of RS will be compared with those from the 6 months preceding the introduction of RS. This information will be obtained from the health agencies’ institutional data. It is worth mentioning that these measures are not a reflection of the CSPs’ effectiveness, given that the CSPs may meet with fewer community members at any given time yet effectively support them in improving their health outcomes. Likewise, given different structures or job tasks across agencies (eg, leading groups, doing outreach, and follow-ups), there might be differences in how these measures are analyzed in the future. The collection of these data will not enable us to detect differences between the intervention and waitlist control groups. We intend to collect these data on the CSP’s delivery of health programming to lay the groundwork for a more in-depth future investigation of the impact of RS.

The measures and tasks used to assess the secondary outcomes are described in the following sentences:

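### Community reach is included in the between-arm ANCOVAs and the d=0.24 statement, although Secondary Outcomes says these data cannot separate the arms, and its after-period has no stated length

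*Protocol article*

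**What the plan says.** The Data Analytic Plan opens its inferential part with "A series of analyses of covariance will be conducted to examine the effects of RS on HRV, health behavior, psychological well-being" and ends the same list with "threats to CSPs leaving the workforce, and the reach of CSPs’ cardiometabolic health programming". The next sentence says outcomes are compared at baseline, after the intervention and "at the 3-month follow-up across participants in the experimental versus waitlist group". No outcome is exempted. The section then states: "With a sample size of 80, it will be possible to detect small-to-moderate effects" ("yielding an effect size *d*=0.24"). It applies this to cardiometabolic health, "threats of CSPs leaving the workforce, and the delivery of cardiometabolic health programming".

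Secondary Outcomes treats reach differently. It is exploratory, it comes from the agencies' institutional data, and it compares the time after RS is introduced with the 6 months before. That section says: "The collection of these data will not enable us to detect differences between the intervention and waitlist control groups".

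Hypothesis 2b in Objectives is also a before/after statement about agencies: "during the period following the introduction of RS as compared with the 6 months preceding the introduction of RS". It nevertheless stands under a lead-in that compares the RS condition with the waitlist condition. Neither section gives the length of the after-period. Hypothesis 2b names absent days, while Table 1 and Secondary Outcomes name days worked.

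**The concern.** One section promises a randomised contrast, with a detectable effect size, for an outcome that another section says cannot provide one. An analyst who follows the Data Analytic Plan literally would report a between-arm effect size for reach. The study's stated purpose is to supply effect sizes for planning a later trial, so that figure could be carried forward as if randomisation supported it.

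The second risk lies in the before/after comparison itself. Days worked, events held and attendance accumulate with observation time. If raw totals are compared over periods of different length, the result reflects period length as well as any change in activity. Absent days and days worked add to this: over a longer period both rise, and one reads as worse and the other as better.

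**Working it through.** **1. The plan's figure.** The inputs in the Data Analytic Plan are N=80 and d=0.24. Power, sidedness and allocation ratio are not stated. I assume 40 per arm, two-sided 5% and 80% power.
- Between arms, detectable d = (1.960 + 0.842) × √(2/40) = 2.802 × 0.2236 = 0.63 (one-sided 0.56).
- Power at d=0.24 is Φ(0.24/0.2236 − 1.960) = Φ(−0.887), about 19%.
- With ANCOVA the detectable d is multiplied by √(1 − r²). Reaching 0.24 needs r = √(1 − (0.24/0.626)²) = 0.92.
- If all 80 participants gave individual before/after values, detectable d = 2.802/√80 = 0.31. Power at 0.24 is about 56% (noncentral t).

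So 0.24 is not reproduced under these assumptions. Whether it is right for the participant-level outcomes is a separate question. Here it matters only that 80 is a count of participants, so the statement presupposes participant-level data compared by arm.

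**2. Does reach have that structure?** The sections compare as follows.
- Contrast: experimental versus waitlist (Data Analytic Plan), against before versus after introduction of RS (Secondary Outcomes, hypothesis 2b).
- Time points: baseline, post-intervention and 3 months, against one 6-month before-period and one after-period.
- Source: participants, against agency institutional records.
- Detectability between arms: claimed, against expressly denied.

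Randomization and Overview assigns individual CSPs and mentions no allocation by agency, so agency totals would normally mix both arms (an inference). The experimental group starts RS 1 week after baseline. The waitlist group starts after 4 + 1 = 5 weeks. The arms therefore differ in exposure for about 5 − 1 = 4 weeks, which is short against a 6-month reference period. The Abstract's ANCOVA sentence names only cardiometabolic health and threats to leaving the workforce, not reach. It is consistent with Secondary Outcomes.

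**3. Effect of the undefined after-period.** If activity runs at a constant rate and RS has no effect, after-total ÷ before-total = after-length ÷ 6 months. The after-lengths below are illustrations, since the article gives none.
- 3 months: 3/6 = 0.50.
- To the 3-month follow-up, counting 4 weeks of sessions, 1 week to the post-assessment and 3 months (13.04 weeks): 18.04/26.07 weeks = 0.69.
- 6 months: 1.00.
- 9 months: 9/6 = 1.50.

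The direction of the artefact thus depends on a length that is not given. Retention is not clearly a count, so I leave it out.

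**The case against.** The strongest reply is that the article already disclaims this outcome. Reach is labelled exploratory in the Abstract, Objectives and Secondary Outcomes. Between-arm detection is denied outright, and the whole study aims at effect sizes rather than significance. The conflict could then be called a loosely written list. This limits the consequence, and no primary conclusion depends on reach. It does not reconcile the text, because the Data Analytic Plan explicitly says an effect on delivery of programming can be detected.

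A second reply is that period length and scaling are details an article may leave to the full protocol or analysis plan. That has force, and the window point is secondary. But the article does fix one side of the comparison at 6 months and leaves the other open.

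A reader might go further and infer that the periods are unequal by plan and that totals would be inflated. Taking October 2022 to May 2024 (Results) as a single after-period gives 19/6, about 3.2-fold. The documents do not support this as the expected result. No after-length is stated, nothing says raw totals will be used, and agencies join throughout enrolment, so 19 months is an extreme. A shorter period would push totals down.

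A reader might also treat the four agencies named in Results as a sample of four and conclude that only a standardised change of about 2.1 is detectable. That assumes exactly four agencies, purely agency-level data and a paired t-test. Further agencies are foreseen, days worked might be recorded per CSP, and no such test is planned.

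Finally, absent days and days worked can be called two views of one thing. That holds only if scheduled days are known and constant, which is doubtful where some CSPs are volunteers.

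**Conclusion.** The contradiction is established from the article's own text. The Data Analytic Plan gives reach a between-arm ANCOVA and a share in the d=0.24 statement, while Secondary Outcomes says the data cannot distinguish the arms. The second description fits the data source and the before/after hypothesis, so neither the randomised comparison nor the detectable effect size should be attached to reach. This conclusion needs no assumption about power or the number of agencies.

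The window point is weaker. The after-period is unspecified, so comparability with the 6-month before-period is not assured. Under a constant rate and unscaled totals, the artefact runs from about 0.5 to 0.7 of the before total for a 3- to 4-month after-period to more than 1 beyond 6 months. Because the outcome is exploratory, this is a correction worth making but not a threat to the trial's main results.

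**What to change.** In the Data Analytic Plan, delete reach from the ANCOVA list and delivery of programming from the d=0.24 sentence. Add one sentence: reach is summarised descriptively before and after introduction of RS, as rates per month (per CSP where the records allow) or over an after-period equal in length to the 6-month before-period, with no between-arm or causal claim. In Objectives, separate hypothesis 2b from the lead-in that compares with the waitlist. Choose either absent days or days worked and use it in Objectives, Table 1 and Secondary Outcomes.

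I would not require the after-period to match the calendar months of the before-period. With introduction in October 2022, the before-period is April to September 2022 and the matched months are April to September 2023, which skips the first 6 months after introduction. For agencies starting after about June 2023, the matched period would run past May 2024.

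The cost is wording and a division by observation time, and the sample size is unchanged. Some data are lost if a longer after-period is truncated. Hypothesis 2b has no randomised test, which Secondary Outcomes already concedes.
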